### Primary Study Parameters

Pain ratings will be collected 4 times a day with a VAS. VAS mean and SD will be reported, and box plots, histograms as well as *P* values for Kolmogorov-Smirnov tests will be evaluated for normality of distribution. A univariate, one-way repeated measures (RM) ANOVA will be conducted with factors group (live music intervention, recorded music active control, and standard care control) by time points (1, 2, 3, 4). The α significance threshold will be .05. The result of interest is the significance of the training×time point interaction, that is, whether the course of the data across time points was altered by the training type. Data are planned with 4 time points; in case of up to 2 missing time points, data will be interpolated [37]. Cases with more than 2 missing time points will be excluded from the analysis. Alternatively, if the residuals of the ANOVA are not normally distributed, a similar Kruskal-Wallis one-way ANOVA will be conducted.

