### Secondary Study Parameters

For metrics that are collected on the same schedule as the VAS (EEG alpha power, delta/alpha power ratio, entropy metrics, HR, respiration rate, and blood pressure), the values per participant will be entered into the same *F* test described for the VAS ratings (as well as correlated with other baseline parameters as described in the “Other Parameters” section). For blood marker metrics that have 2 data collection points, a similar RM ANOVA will be conducted, but with 2 as opposed to 4 measures, and a significant interaction between treatment and time point would indicate whether treatment significantly impacted the amount of the neuroinflammatory blood marker. Categorical incidence metrics (delirium and POCD) will be evaluated with a one-way ANOVA to determine whether treatment impacted these neuroinflammatory-related complications. Delirium and signs of delirium will be perceived using the DOSS. The DOSS is a screening instrument for delirium, consisting of 13 items, and will be filled by a registered nurse during hospital admission until discharge. Nurses have frequent contact with the patients and are in a good position to observe behavior changes 24 hours a day when patients are admitted. The DOSS is already part of a routine in the surgical wards and all registered nurses are already trained. Likewise, scalar pain medication dosage will be averaged over 24-hour periods per patient and entered into a chi-square test to determine whether the dosage was significantly different across the 3 treatment groups. As this is exploratory and serves to inform future hypothesis-directed testing, we will not correct for multiple comparisons.

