#### Power

The sample size was calculated using G*Power 3.1 [38], an industry-standard software. Below, we explain the parameters for an RM between-subjects univariate ANOVA as well as the final sample size. The calculation was based on the desired ability to detect a within-between interaction (intervention group×time point), with recommended internal settings from [39], which would effectively indicate whether the live music intervention altered the slope of outcome measurements compared to the recorded music or do-nothing control groups.

The effect size (partial η^2^=0.051, converted to f=0.2318206) was determined from a retrospective RM ANOVA with published data [1].

Alpha: As we have a single quantitative outcome measure, alpha may remain at the conventional .05 significance threshold.Power: Following recent recommendations to set power above the typical 0.8 to 0.9 and higher [40], the threshold was set at 0.9.Number of groups or measurements: The design calls for 3 groups, with 4 RM (see “Study Design” section; before treatment, after treatment, 3-hour, and 6-hour follow-up) for each participant.Nonsphericity correction: As mentioned earlier, retrospective analyses were conducted with the data published in [1]. The ANOVA conducted with that data passed the assumption of sphericity (*P*=.07); therefore, no correction (1) was entered in the G*Power calculation.Sample size: The sample size (n=327, Table 3) outputted from G*Power represents the total number of participants in a 3-group design required to achieve 0.9 power with an effect size of ~0.232-109 per group. Padding for a 10% dropout rate raises the per group n to 120, for a total N of 360.

**Table 3 table3:** G*Power sample size calculation.

Parameters			Value

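### The primary test enters the pre-session VAS as an outcome level, not as a covariate: the stated power is right for that test, but efficiency is lost and chance baseline differences feed into the result

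*Protocol article*

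**What the plan says.** In the Protocol article, Primary Study Parameters, the VAS ratings go into an ANOVA "with factors group (live music intervention, recorded music active control, and standard care control) by time points (1, 2, 3, 4", and the group by time interaction is the result of interest. No covariate is named.

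The Power section identifies the four levels: "4 RM (see “Study Design” section; before treatment, after treatment, 3-hour, and 6-hour follow-up) for each participant". Table 1 likewise places a VAS rating at 10:30 AM, ahead of the session. Level 1 is therefore a pre-treatment measurement.

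The secondary analyses follow the same form. For measures on the VAS schedule, "the values per participant will be entered into the same *F* test described for the VAS ratings". For the blood markers, "a similar RM ANOVA will be conducted, but with 2 as opposed to 4 measures".

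Baseline parameters appear as covariates only in the post hoc analyses (Other Study Parameters, in the statistical part). The list of those parameters covers comorbidities, complications, postoperative days, surgery characteristics, musical background, age and cognition. It does not include the pre-session VAS.

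Treatment Allocation explains that arms are set by a calendar fixed in advance, that comparability relies on chance in surgery scheduling, and that consent comes before the treatment is disclosed.

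**The concern.** With baseline as an outcome level, the interaction asks whether the arms share the same three differences from the pre-session rating. That fixes the slope of later pain on starting pain at 1 instead of estimating it. Whenever the correlation between ratings is below 1, this leaves noise in the comparison that the collected data could remove.

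It also leaves regression to the mean in the comparison. If one arm happens to recruit patients with more pain, their ratings tend to drift back and the drift looks like a treatment effect. Here patients arrive in calendar weeks, about 8 data sets per treatment period, from mixed surgery types, so differences in starting pain are plausible.

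At stake are the precision of the primary comparison and how its result can be read if the arms start apart.

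**Working it through.** **Inputs from the article.** "The α significance threshold will be .05"; for power, "the threshold was set at 0.9"; effect size "converted to f=0.2318206"; "The design calls for 3 groups", with 4 measurements; ε = 1; N = 327 (Table 3). **Assumed:** a common correlation ρ between ratings, 0.3 to 0.9, because the article gives none. Compound symmetry is used, which is consistent with ε = 1.

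**1. The plan's own figure.** λ = f² × N = 0.2318206² × 327 = 17.573. df = (3−1)(4−1) = 6 and (327−3) × 3 = 972. Critical F = 2.108, power = 0.9008. This matches Table 3.

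**2. Planned test.** An effect equal at all post ratings has pattern (0, 1, 1, 1). Its centred sum of squares is 0.75² + 3 × 0.25² = 0.75, so λ is proportional to 0.75/(1−ρ). An effect only directly after the session, (0, 1, 0, 0), also gives 0.75.

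**3. Adjusted test.** Given the pre-session rating, and with expected baselines equal, the three post ratings have covariance (1−ρ)(I + ρJ), where J is the matrix of ones. Testing group and group × time jointly also uses 6 df. λ is proportional to:
- lasting effect: 3/[(1−ρ)(1+3ρ)]
- immediate-only effect: (1+2ρ)/[(1−ρ)(1+3ρ)]

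**4. Ratio of adjusted to planned λ.** Lasting: 4/(1+3ρ). Immediate-only: (4/3)(1+2ρ)/(1+3ρ). Multiplying 17.573 by the ratio, with 6 and roughly 970 df:

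| ρ | Lasting: ratio | power | Immediate-only: ratio | power |
|---|---|---|---|---|
| 0.3 | 2.105 | 0.999 | 1.123 | 0.935 |
| 0.5 | 1.600 | 0.990 | 1.067 | 0.921 |
| 0.7 | 1.290 | 0.965 | 1.032 | 0.911 |
| 0.9 | 1.081 | 0.925 | 1.009 | 0.904 |

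An effect fading as 1 : 0.67 : 0.33 gives 0.973 at ρ = 0.5 and 0.946 at ρ = 0.7. The comparison value throughout is 0.901.

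**5. No treatment effect, but one arm starts 0.3 SD higher.** With 109 per arm, the sum of squares between arms is 109 × (2/3) × 0.3² = 6.54.
- *The difference regresses to the mean.* The planned test gets λ = 6.54 × 0.75 × (1−ρ), which is 2.45 at ρ = 0.5 and 1.47 at ρ = 0.7. Its false-positive rate is about 0.17 (0.16 in simulation) and 0.12. The adjusted test stays near 0.05.
- *The difference persists at all four ratings.* The planned test stays near 0.05. The adjusted test leaves a bias of 0.3 × (1−ρ) SD, so λ = 6.54 × 3(1−ρ)/(1+3ρ), which is 3.92 at ρ = 0.5 and 1.90 at ρ = 0.7. Its false-positive rate is about 0.26 to 0.30 (formula and simulation) and 0.14.

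These rates are conditional on a 0.3 SD imbalance. For independent patients that is large: the standard error of one arm against the other two is √(1/109 + 1/218) = 0.117 SD, so 0.3 is about 2.6 standard errors. Without imbalance, both tests hold close to 0.05.

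**6. Two-point blood markers.** The interaction is the same as a test of raw change. The adjusted variance is (1+ρ)/2 of the change-score variance: 25% lower at ρ = 0.5 and 15% lower at ρ = 0.7.

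**The case against.** The strongest objection is that allocation is not randomised. If case mix makes one arm persistently more painful, change from baseline removes the shift and covariate adjustment removes only part of it. Step 5 shows the cost, and neither model is better in every case. This stands, and it is why the planned interaction must be reported too.

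Its force as a reason to leave the plan alone is limited. The calendar is fixed in advance, consent precedes disclosure of the treatment, and the article itself relies on chance scheduling. If persistent case-mix variation arises week by week (assumed intraclass correlation 0.02 to 0.10, 15 weeks per arm), simulation puts the adjusted test's false-positive rate at only about 0.06 to 0.09.

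Two further objections stand. The gain depends on a correlation the article does not give and on how long the effect lasts. The planned test is also the one that was powered. The adjusted joint test asks a somewhat different question: whether the arms differ at any post-session time, not whether the course over time was altered.

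Some stronger readings are not supported:
- *That the interaction wastes degrees of freedom on baseline.* The replacement also has 6 df.
- *That live versus recorded music suffers most.* Under this model the variance ratio is the same for every pair of arms.
- *That a test of the average post rating shows the size of the gain.* Such a test has 2 df, and a 2-df change-score test with no covariate already reaches 0.970 for a lasting effect. Part of that gain is due to fewer df.

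**Conclusion.** The point holds as one of efficiency and of sensitivity to chance baseline differences. A reader might infer an underpowered trial or a wrong sample size. The article does not support that, because N = 327 and power 0.90 reproduce exactly for the test chosen.

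On the article's premise of chance baselines, the adjusted 6-df test has power from about 0.90 (immediate-only effect, ρ = 0.9) to 0.99 or more (lasting effect, ρ of 0.5 or lower). It did not fall below the planned test in any scenario computed. The result rests on compound symmetry, an assumed ρ, and equal expected baselines. If imbalance is systematic and persistent, the ordering reverses and the adjusted test is the biased one. For the secondary measures the point is minor, since the article calls those analyses exploratory and claims no power for them.

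**What to change.** In Primary Study Parameters, prespecify a repeated measures model of the three post-session ratings (directly after, 3-hour, 6-hour). Include group, time, group × time, pre-session VAS and pre-session VAS × time, and test group and group × time jointly.

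State in the same place:
- that the baseline is the rating before the first session, because from day 2 the pre-session rating follows earlier sessions;
- which day's post-session ratings are analysed;
- how a missing baseline is handled, since the current rule allows up to two missing time points;
- that the model relies on baselines differing only by chance;
- that the planned four-level interaction is reported beside it, and that disagreement between the two will be discussed as possible systematic imbalance.

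The same form may be used for the exploratory secondary measures, including baseline-adjusted ANCOVA for the blood markers. The sample size can stay, with 0.90 described as the power of the unadjusted interaction.

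The change needs a short paragraph of analysis text and no new patients, visits or measurements. It should be made before the preliminary analysis announced in Results. The cost is exposure to persistent imbalance, which the parallel analysis makes visible but does not remove.

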**Results:**

At study completion, we will have an empirical indication of whether live music or recorded music has a significant impact on postoperative perceived pain. We hypothesize that the live music intervention will have more impact than recorded music but that both will reduce the perceived pain more than care-as-usual. We will moreover have the preliminary evidence of the physiological underpinnings responsible for reducing the perceived pain during a music intervention, from which hypotheses for future research may be derived.

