**Conclusions:**

Live music can provide relief from pain experienced by patients recovering from surgery; however, it is not known to what degree live music improves the patients’ pain experience than the logistically simpler alternative of recorded music. Upon completion, this study will be able to statistically compare live versus recorded music. This study will moreover be able to provide insight into the neurophysiological mechanisms involved in reduced pain perception as a result of postoperative music listening.

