Therefore, further secondary outcomes will explore behavioral indicators (postoperative cognitive decline or POCD and delirium) and biological markers (interleukin-6 [IL6], C-reactive protein [CRP], neutrophil gelatinase–associated lipocalin [NGAL], and translocator protein [TPSO]) with established neuroinflammatory underpinnings [16-20] to see whether the primary pain outcome has a statistical relationship to these neuroinflammatory-related metrics. The exploratory electroencephalogram (EEG) analyses will also be conducted to see whether either entropy [21], alpha power [22], or delta/alpha power ratio [23,24] can provide neuroinflammatory markers, which could correlate with postoperative pain outcomes. Finally, we will explore whether these neuroinflammatory markers seem to be mitigated by either the live music or active control intervention to explain the reduced pain reported by postsurgical patients in music intervention studies [2,20].

The primary objective is to see whether a live music intervention reduces pain perception compared to both recorded music active control and standard care control groups. The secondary objective is to explore the role of music in mitigating the neuroinflammatory response to surgery, for future hypothesis-directed research.

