## Discussion

### Principal Findings

Previous studies have shown that postoperative pain management can be supplemented with music intervention. Yet, little is known about the benefits of live versus recorded music, or what physiological mechanisms may be mitigating pain perception as a response to listening to music. This NCT will compare the MiMiC live music intervention with listening to recorded music and care-as-usual. The primary objective is to see whether pain VAS ratings differ across the 3 conditions, and the secondary objective is to see whether postoperative neuroinflammation is reduced as a response to listening to music.

The strength of this study is the inclusion of preoperative assessments to establish some baseline characteristics of patients. First, the preoperative musical background questionnaire (selected items from [30]) assesses the estimated weekly hours of music listening as well as listening preferences for musical genre and whether or how the participant is musically trained. This provides us the opportunity to analyze how the extent of musical exposure may affect the primary outcome (pain VAS) of the intervention; depending on the strength of these findings, we may be able to even help inform future music interventions according to preoperative musical habits. Second, the preoperative cognitive assessment (6CIT) [28] serves as an important baseline for several secondary outcomes that may help to account for variability among the 3 intervention arms that otherwise might be attributed to the treatment. Specifically, the 6CIT will inform the interpretation of the postoperative cognitive status, and it may predict alpha power in EEG recording [22] that in turn may be linked to delirium [23,24]. If this proves to be the case, the preoperative cognitive status might be investigated in the future as a method to inform more at-risk patients who could especially benefit from supplementary nonpharmacological interventions [41] such as live or recorded music [42].

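### The primary group×time F test on 6 df has no direction and names no pair, so on its own it cannot show that live music beats recorded music and standard care

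*Protocol article*

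**What the plan says.** All references are to the Protocol article.

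- **Objective.** The Introduction asks "whether a live music intervention reduces pain perception compared to both recorded music active control and standard care control groups". The Objective paragraph of the Abstract says the same in substance.
- **Hypothesis and promise.** The Abstract's Results paragraph expects that the "live music intervention will have more impact than recorded music but that both will reduce the perceived pain more than care-as-usual". Its Conclusions paragraph says that "this study will be able to statistically compare live versus recorded music".
- **Primary test.** Primary Study Parameters specifies group (3) by time point (4) and states: "The result of interest is the significance of the training×time point interaction". It adds: "The α significance threshold will be .05". The Kruskal-Wallis fallback in the same section is also an overall test of three groups.
- **Reading of the test.** The Power section says the interaction would in effect indicate "whether the live music intervention altered the slope of outcome measurements compared to the recorded music or do-nothing control groups".
- **Sizing.** Table 3 gives numerator df 6, denominator df 972, 327 participants (109 per group) and power 0.9008, all for this interaction.
- **A second wording of the objective.** Principal Findings in the Discussion states: "The primary objective is to see whether pain VAS ratings differ across the 3 conditions". This wording has no direction and no pair.

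**The concern.** The objective needs two directional statements to be true together: live lower than recorded, and live lower than standard care. The interaction test asks only whether the three daily profiles are parallel. It can be significant because recorded music alone works, because both kinds of music work equally well, because live music is worse, or because the profiles differ in shape only. The Power section therefore attributes to the F test a conclusion it cannot give.

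The live-versus-recorded comparison is the one the article presents as its contribution, and its closing Conclusions say it can inform policy makers. A primary result could be positive while that comparison is null or goes against live music. A reader could also carry the 0.9 power over to a comparison for which it was not calculated.

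**Working it through.** **1. Reproduce the plan's figure.** Inputs from the Power section and Table 3: partial η² = 0.051, k = 3 groups, m = 4 measurements, ε = 1, α = .05, N = 327.

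- f = √(0.051/0.949) = 0.23182, so f² = 0.05374.
- λ = f² × N = 0.05374 × 327 = 17.573.
- df1 = (3−1)(4−1) = 6; df2 = (327−3)(4−1) = 972.
- Critical F = 2.1079; power = 0.9008.

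Table 3 reproduces exactly. N = 326 gives 0.8998, so 327 is the minimum.

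**2. Live equal to recorded, both better than standard care.** The documents do not say how many groups were in the retrospective ANOVA that supplied η², so both readings are shown.

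- *Planning effect from a two-group contrast δ:* the variance of the group means is δ²/4 with two groups and 2δ²/9 with three groups when two of them coincide. The ratio is (2/9)/(1/4) = 8/9. Then λ = 8/9 × 0.05374 × 327 = 15.62, and the power of F(6, 972) is 0.857.
- *Planning effect as the three-group effect:* λ stays at 17.573 and power is 0.90.

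On either reading the true live-recorded difference is zero.

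**3. Other patterns, omnibus λ held at 17.573.** The patterns are assumptions, because the documents give no pairwise effect. For a pair with standardised difference d, λ = (109/2) × d², on 3 df (group×time for that pair) or 1 df (a single contrast that captures the whole effect), with 972 error df and α = .05. For equal spacing (−d, 0, d) the variance is 2d²/3 = f², so d² = 1.5 × 0.05374 = 0.0806. Live versus recorded then has λ = 54.5 × 0.0806 = 4.39.

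| Pattern | Omnibus | Live vs recorded, 3 df | Live vs recorded, 1 df | Live vs standard care, 3 df |
|---|---|---|---|---|
| Live < recorded < standard care, equal spacing | 0.90 | 0.39 | 0.55 | 0.95 |
| Live = recorded, both better than standard care | 0.90 | 0.05 (true difference zero) | 0.05 | 0.87 |
| Live better, recorded = standard care | 0.90 | 0.87 | 0.95 | 0.87 |
| Recorded better, live = standard care | 0.90 | 0.87 (against live) | 0.95 (against live) | 0.05 (true difference zero) |

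The omnibus power is the same in every row, including the two in which the stated objective is false. In 20,000 simulated trials under equal spacing, about 58% of significant omnibus results came without a significant live-versus-recorded contrast (3 df). About 38% of trials had the omnibus and both live contrasts significant.

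**4. Choice of contrast over time.** Suppose the effect appears only directly after the session, with profile (0, d, 0, 0) and equally correlated ratings. The interaction signal is d²(1 − 1/4) = 3d²/4. The mean of three post-session ratings minus the pre-session rating has value d/3 and squared length 1 + 3 × (1/9) = 4/3, so its signal is (d²/9)/(4/3) = d²/12. The ratio is (1/12)/(3/4) = 1/9.

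**The case against.** The strongest defence is that an omnibus test followed by pairwise tests is standard practice. With three groups, an omnibus gate followed by unadjusted pairwise tests is a recognised closed procedure that controls the familywise error. A condensed article may leave those follow-up tests to the full protocol or the analysis plan, neither of which is shown. This stands. A reader might infer that any live-versus-recorded claim will rest on tests picked after the data are seen. The article does not support that, because it is silent on follow-up contrasts and they may be fixed elsewhere. The point rests on what the article states: the interaction as the result of interest, the trial sized on it, and a reading of it as specific to live music.

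Second, the wording in Principal Findings does fit an omnibus test. This also stands, but that wording conflicts with the Abstract and Introduction, so it is a further reason to reconcile them.

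Third, group means and SDs will be reported, so direction will be visible. That is true, but a visible direction is not a test of it.

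Fourth, a rejection when live equals recorded is not an error, since both music arms then do beat standard care. This is correct. The 0.86 to 0.90 should not be read as a false-positive rate. It is the chance of a positive primary result when the live-versus-recorded part of the objective is false.

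**Conclusion.** The point holds in this form. The named primary test cannot by itself answer the objective in the Abstract and Introduction, and the Power section states wrongly what the test would show. It does fit the looser objective in Principal Findings.

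If live equals recorded and both beat standard care, the test is significant with probability 0.86 or 0.90, depending on whether the planning η² came from two groups or describes three. The 0.9 power applies only to the omnibus test.

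A reader might go further and conclude that the trial is underpowered for its pairwise questions. The documents do not establish this. Power for live versus recorded on 3 df is 0.39 under equal spacing but 0.87 if recorded music does no better than standard care, and the article gives no pairwise effect from which to choose between them.

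**What to change.** 1. State one primary objective and use it in the Abstract, the Introduction and Principal Findings. Correct the Power section so that it no longer says the interaction is specific to live music.
2. Before any comparative data are analysed, make live versus standard care and live versus recorded the prespecified group×time contrasts, from the same model, that decide the primary claim. Attach a rule that controls error, for example a fixed sequence, or both required at two-sided .05. If the full protocol or analysis plan already contains such contrasts, align the primary analysis with them.
3. Claim that live is better than both only if both contrasts succeed in the right direction. Report both differences with 95% CIs. Keep the omnibus interaction as a gate or as supportive evidence.
4. Fix the time-point form of the contrasts in advance. Averaging the three post-session ratings is one option, but it keeps only 1/9 of the interaction signal if the effect is immediate only, and so loses most of its power.

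**Cost.** No extra data collection, but more than a change of wording. Recruitment began in June 2022, so this is an amendment to a running trial. The power statement must also change: at 109 per group, live versus recorded has about 39% (3 df) to 55% (1 df) under the assumed equal spacing. Reaching 90% under that assumption would take 353 per group (1,059 in total) on 3 df or 261 per group (783 in total) on 1 df, before dropout. Against a planned 360 over 4 years, it is more sensible to restate the power for this contrast openly than to enlarge the trial.

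### Interpolating up to two of a patient's four pain ratings can dilute a short-lived effect and, if missingness differs by arm, can create a false group-by-time interaction

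*Protocol article*

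**What the plan says.** Under Primary Study Parameters, pain is rated on a 0-10 VAS four times a day and analysed by repeated measures ANOVA with group (live, recorded, standard care) and time point (1 to 4). The interaction is the result of interest: "whether the course of the data across time points was altered by the training type". "The α significance threshold will be .05".

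The same paragraph fixes the handling of gaps: "in case of up to 2 missing time points, data will be interpolated", and "Cases with more than 2 missing time points will be excluded from the analysis". The rule does not distinguish inner time points from the first and last.

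Table 1 puts the ratings at 10:30, about 11:00 (end of the session), 14:00 and 17:00, so spacing is unequal. Under Power, "The design calls for 3 groups, with 4 RM" and "no correction (1) was entered in the G*Power calculation"; the calculation assumes four ratings from every patient. The 10% padding is for dropout. No expected share of missing single ratings is given, and nothing elsewhere in the article modifies the rule.

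**The concern.** The interaction test asks whether the shape of the four-point course differs between groups. Interpolation imposes a straight line wherever a rating is absent. If the gap is the post-session rating, the immediate response is replaced by a value lying between the pre-session and 3-hour ratings. If ratings 2 and 3 are both absent, the whole middle of the course becomes a line from the first rating to the last.

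Two consequences are possible. A real but brief effect may be diluted, which costs power. If gaps are commoner in one arm, and pain dips or rises after the session in all arms alike, the filled values shift that arm's mean and mimic an interaction.

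There is also a logical gap. A first or last rating has no neighbour on one side, so interpolation cannot produce it, yet the rule as worded covers it. Whatever is used there is extrapolation.

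**Working it through.** **1. The plan's own figure.** Inputs from Power and Table 3: partial η² = 0.051, "converted to f=0.2318206", 3 groups, 4 measurements, ε = 1, α = .05, and for power "the threshold was set at 0.9".
- f = √(0.051/0.949) = 0.2318
- λ = f² × N = 0.05374 × 327 = 17.573
- df = (3−1)(4−1) = 6 and (327−3)(4−1) = 972
- critical F = 2.1079, power = 0.9008

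The stated 327 (109 per group) reproduces exactly, for four complete ratings per patient.

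**2. What a filled post-session rating contains.** Assumed true live-versus-control effects: 0 at 10:30, −1.0 at 11:00, −0.5 at 14:00.
- Filled by time-point order: (0 + (−0.5))/2 = −0.25, so 25% is kept.
- Filled by clock time: weight on 14:00 is 0.5 h/3.5 h = 1/7, giving −0.5/7 = −0.071, so 7% is kept.

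**3. Effect on the trial mean.** With share p missing equally in all arms, the mean effect is (1−p)(−1.0) + p × (filled value). The article gives no p, so a range is shown.

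| p (assumed) | by order | by clock | loss |
|---|---|---|---|
| 10% | −0.925 | −0.907 | 7.5-9% |
| 20% | −0.850 | −0.814 | 15-19% |
| 30% | −0.775 | −0.721 | 22.5-28% |

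**4. False difference with no true effect.** Assumed common course 4.0, 3.4, 4.2. The filled value is 4.1 by order or 4.0 + 0.2/7 = 4.03 by clock, so it exceeds the true 3.4 by 0.70 or 0.63.
- 30% versus 10% missing: 0.20 × 0.70 = 0.14, or 0.20 × 0.63 = 0.13 points.
- A 5-point gap in missingness: 0.05 × 0.70 = 0.035, or 0.05 × 0.63 = 0.03 points.

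**5. Simulation, 109 per group.** Assumptions: compound symmetry, effect scaled to λ = 17.57, recorded music at half the live effect, linear filling (by order or clock), end gaps taking the nearest observed rating. There were 500 runs per power scenario and 1000 per null scenario. Monte Carlo error is about ±0.015 at α and up to ±0.04 for power. The comparator is the same interaction test on observed ratings only, with patient effects.

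Power when the effect is confined to the post-session rating and that rating is missing equally (0.92 with complete data):

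| missing | interpolated | observed only |
|---|---|---|
| 10% | 0.85 | 0.89 |
| 20% | 0.76-0.78 | 0.84 |
| 30% | 0.63-0.65 | 0.75 |
| 50% | 0.36 | 0.59 |

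Type I error when all groups share a dip of 1 within-patient SD at rating 2 and half that at rating 3, with either the post-session rating or the last two ratings missing:

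| missing by group | interpolated | observed only |
|---|---|---|
| 0/10/20% | 0.08-0.12 | 0.05 |
| 0/0/30% | 0.20-0.30 | 0.05-0.06 |
| 20/20/20% | 0.05-0.06 | 0.06 |

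With half that dip, the 0/0/30% case gives 0.07-0.10 under interpolation.

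**6. Other effect shapes.**
- Fading effect, last two ratings missing in 50% and the last rating carried forward: power 0.95, against 0.91 with complete data. The fading effect is made to look lasting.
- Constant effect at ratings 2 to 4, post-session rating missing in 10-50%: power 0.86-0.88, against 0.89 with complete data. Almost nothing is lost.

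**The case against.** Several stronger readings are tempting, and the article does not support them.

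- *That the rule always biases the effect toward zero when missingness is even.* It does not. Direction and size depend on which rating is missing and on the shape of the effect: a lasting effect loses almost nothing, and a carried-forward last rating can exaggerate a fading one.
- *That control patients would miss more post-session ratings because nobody visits them.* Table 1 has one 10:40-11:00 row for live, recorded and no intervention alike, with the same measurements at its end, so control patients also have a planned contact then. Unequal missingness remains possible in an open, nonrandomized design, but the article gives no specific reason to expect it.
- *That counting filled values materially inflates the error degrees of freedom.* Removing about 65 values (20% of 327) takes 972 to about 907 and moves critical F from 2.1079 to 2.1086, which is negligible.
- *That excluding patients with a single rating is costly.* One rating carries no within-patient change, so it adds little to this test.
- *That 75-93% of the effect is lost.* That holds per filled value, for patients whose post-session rating is missing, and not for the trial mean.

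It is also fair to say that the reference cited for interpolation is not at hand, so linear filling is an inference, and that handling of end points could be detailed in an analysis plan. What stands is that the article commits the primary endpoint to filling ratings before a test of their course, and that no form of interpolation proper can supply an end point.

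**Conclusion.** The rule is poorly matched to the hypothesis it serves. It can dilute a short-lived effect when the post-session rating is missing, by more than the missing data alone would: at 20% missing, simulated power is 0.76-0.78 against 0.84 on observed ratings only. It can raise type I error when missingness differs by arm and the common pain course is non-linear, to 0.08-0.12 or 0.20-0.30 in the two unequal scenarios with the larger dip. With equal missingness the error stays near 0.05. First and last ratings fall outside what interpolation can do.

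All of these sizes rest on assumed missingness rates, effect shapes and linear filling. The article states no missingness rate, so the harm in this trial cannot be fixed and could be small if few ratings are lost. The case for change is that a better method is available at almost no cost.

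**What to change.** Delete the interpolation and exclusion rules under Primary Study Parameters. Analyse all observed ratings with a likelihood-based mixed model with categorical time and a group-by-time interaction, using a covariance structure that handles both the four ratings within a day and their repetition over up to 5 days. This fills nothing, keeps every patient with any rating, and is valid if ratings are missing at random.

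Add one sensitivity analysis for ratings not missing at random, for example delta-adjusted multiple imputation by arm. Ordinary multiple imputation would not serve, because it usually rests on the same missing-at-random assumption as the mixed model.

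Secondary Study Parameters sends EEG measures, heart rate, respiration rate and blood pressure through the same F test, so state whether the new handling applies there too.

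The cost is analysis wording and some programming. No extra patients or data are needed, and with data collection expected to run to 2026 the change can be made before the analysis.
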